#### Secondary Outcomes

Descriptive statistics of the study participant characteristics at baseline and questionnaire responses will include means, SDs, frequencies, and percentages according to the type of variable (continuous or categorical). The fit of quantitative variables to the normal distribution will be confirmed by the Shapiro-Wilk test. Differences in demographic information at baseline between groups will be analyzed using the chi-square test for categorical variables and ANOVA or the 2-tailed *t* test for continuous variables (ie, age, sex, employment status, educational attainment, previous meditation experience, and psychological distress at baseline).

#### Other Analyses

An interim analysis will be conducted once half of the planned number of participants have completed the intervention period. The interim analysis will primarily examine the feasibility, including dropout rates, and the trial may be discontinued if the dropout rate is higher than expected. Multivariate analysis will be conducted to test the effects of the interventions, adjusting for estimated predictors or confounding variables, and multilevel linear regression will be performed.

Following the intention-to-treat principle, the analyses will include data from all participants. Web-based self-care interventions are often associated with higher dropout rates and lower rates of continued implementation [86]. In their study, Farvolden et al [87] reported that only 12 of 1161 participants (approximately 1%) completed a 12-week web-based panic disorder self-help program in its entirety. Similarly, Hasselberg and Rönnlund [83] conducted a 2-week web-based program targeting mindfulness and self-compassion and reported that 33% of the participants stayed in the program until the end. Therefore, even if self-care app activities are minimal, participants will be considered to have completed the course and will be included in the analysis if each questionnaire is answered. The patterns of missing values will be examined and, when applicable, replaced with suitable statistical methods.

### Adverse Event Reporting and Harms

The participants in this study comprise a nonclinical population with lower than a certain level of psychological distress and no diagnosed mental disorders. Therefore, the risk associated with psychological interventions is assumed to be low. Participants may interrupt a trial without disclosing the reason and will be able to contact the research staff via email or web-based forms, if necessary. Participants can also obtain information on mental health services operated by public institutions on web-based forms and receive mental health care as needed.

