### Criteria for Discontinuing or Modifying Allocated Interventions

In this study, only participants with psychological distress below a certain level will be included; thus, the risks associated with the intervention are likely to be minimal. However, we will provide information on support groups or mental health services that participants can contact in case they experience any distress. Participants can discontinue the trial at any time without providing further explanation.

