### Outcomes: Primary Outcome Measures

#### Psychological Distress

Psychological distress will be assessed using the Japanese version of K6 [40,41]. All items are rated on a scale ranging from 0=never to 4=always over the past 30 days. It has been designed to assess nonspecific psychological distress (depressive mood and anxiety) using 6 items. The reliability and validity of the Japanese version have been reported to be equal to those of the original English version [41]. A previous study suggested a cutoff point of 12 or 13 for K6 scores to screen for severe depressive symptoms [42]. Considering the possibility of a high psychological burden for participants with severe depressive symptoms, we set an exclusion criterion of a K6 cutoff value of 13 or higher, from an ethical point of view.

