### Assignment of Interventions: Blinding

It is practically impossible to blind the allocation in this study because the participants engage in the meditation independently, following a guide. Therefore, this study will be an open-label RCT. Once a participant is assigned to a condition, there will be no further interaction with the research staff, except when the participant contacts the research staff. To minimize interaction between the participants and research staff, notifications and instructions will be sent to the participants via automated emails. Participants can infer which group they have been allocated to, based on the instructions, but they are not explicitly informed about the groups to which they are assigned.

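### Harms rest on participant-initiated contact alone, so individual adverse effects will probably be under-counted and a low count could not be read as safety

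*Protocol article*

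**What the plan says.** The protocol article has its own section, Adverse Event Reporting and Harms. It argues from the population (non-clinical, distress below a set level) that "the risk associated with psychological interventions is assumed to be low". It then says that "Participants may interrupt a trial without disclosing the reason" and that participants "will be able to contact the research staff via email or web-based forms, if necessary". The rest points to public mental health services. The section gives no definition of an adverse event, no question that elicits one and no comparison between arms. It does not say how a message from a participant would be recorded.

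Three other sections bear on this:

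- Criteria for Discontinuing or Modifying Allocated Interventions: "Participants can discontinue the trial at any time without providing further explanation".
- Assignment of Interventions: Blinding: once a participant is allocated, "there will be no further interaction with the research staff, except when the participant contacts the research staff".
- Other Analyses: "The interim analysis will primarily examine the feasibility, including dropout rates", and "the trial may be discontinued if the dropout rate is higher than expected". No harm-related ground for discontinuing the trial is stated.

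Worsening can also be seen through the outcomes. "Psychological distress will be assessed using the Japanese version of K6", a primary outcome, and it is scheduled in all arms at baseline, 1 month and 2 months. Perceived stress and somatic symptoms follow the same schedule.

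**The concern.** A participant whom the meditation makes worse reaches the harms record only by deciding to write in. If that person stops and also leaves the questionnaire unanswered, the trial sees a dropout with no cause attached.

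The trial is meant to inform self-care content for healthy workers, a setting in which even modest harm matters to the balance of benefit and risk. A short list of spontaneous reports would look like support for the low-risk assumption, although the plan has no method for testing it.

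**Working it through.** **1. What is scheduled.** Table 1 lists 15 rows at baseline, post and follow-up, two weekly measures and two daily ones. They cover demographics, symptoms, traits, work outcomes, affect, relaxation and heart rate. None asks whether the practice had unwanted effects. In weeks 1 to 4 the weekly and daily measures apply only to the two active arms, so they have no concurrent waitlist comparison.

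**2. Denominators.** The plan's sample size reproduces. For a time-by-group interaction with 3 groups, 2 occasions, f = 0.15, correlation 0.5 and alpha 0.05, the noncentrality is f² × N × 2/(1 − 0.5), with 2 and N − 3 degrees of freedom. The smallest N with 80% power is 111, or 37 per arm (power 0.803). The two active arms hold 67 + 67 = 134 at randomisation. With 40% attrition, about 0.60 × 67 = 40 per arm return the post assessment, that is, 80 active against 40 waitlist.

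**3. Chance of no report under passive capture.** The documents give neither a harm rate h nor the share s of harmed participants who write in; both are assumed. With independent participants, P(no report) = (1 − h × s)^134.

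| h | s = 5% | s = 10% | s = 25% | s = 50% |
|---|---|---|---|---|
| 5% (6.7 expected harms) | 0.72 | 0.51 | 0.19 | 0.03 |
| 10% (13.4 expected harms) | 0.51 | 0.26 | 0.03 | 0.001 |

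The Results section reports 375 enrolled. If two-thirds of these were in active arms (375 × 2/3 = 250), h = 5% and s = 10% would give 0.995^250 = 0.29. Whatever the size of the trial, the expected number of reports is only the fraction s of the true harms, and s is unknown.

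**4. What the scores can show.** The Primary Outcome section analyses participants with pre and post assessments by repeated measures ANOVA, which compares means. Someone who leaves distressed without a post questionnaire adds no post score. Among those who stay, a harmed minority is diluted: if 5 of 40 completers rise by 5 K6 points, the arm mean moves by 5 × 5/40 = 0.6 points, which improvement in the others can offset. No analysis of individual worsening is described.

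**5. What a count of worsened participants would add.** I used the two-sided 5% normal approximation for two proportions: power = Φ[(d − 1.96 × SE0)/SE1], where d is the difference, SE0 the pooled and SE1 the unpooled standard error. The proportions are assumed.

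| Worsened, waitlist vs active | 66 vs 134 | 40 vs 80 |
|---|---|---|
| 5% vs 15% | 0.55 | 0.34 |
| 5% vs 20% | 0.85 | 0.60 |

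Such a table can expose a large difference. At planned size it cannot rule out a moderate one, so it belongs in the report as an estimate with a confidence interval.

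**The case against.** The strongest reply is that the trial does measure deterioration. K6, perceived stress and somatic symptoms are collected in every arm, and the waitlist answers its 1-month form before it starts the app, so the comparator is unexposed. Active participants also report negative affect weekly and rate relaxation before and after each meditation. Stopping the app is not the same as leaving the study: Other Analyses keeps people with minimal app use if they answer the questionnaires, and the gift card depends on participation. A distressed participant may well still return a K6.

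This stands in part. A reader might infer that the trial is bound to find no harm, or that recorded harms must be near zero. The documents do not support that: mean worsening could appear, and section 3 of the working shows that at least one report is likely under some of the assumed rates. What remains is that scores work mainly through completers' means and do not attribute an effect to the practice.

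Other stronger readings also fail:

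- A reader might infer that leavers are never asked why. The text says only that they need not say.
- A reader might infer that the dropout trigger cannot respond to harm, or that dropout is examined only in total. Neither is stated. If 5 extra people left each active arm on top of the expected 40%, overall dropout would be (80 + 10)/200 = 45%, above expectation. The trigger cannot show why they left.
- A reader might infer that dropout is all the interim looks at. The text says primarily, so dropout is the only stated trigger but perhaps not the only content.

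Finally, a journal article condenses a fuller protocol, and adverse event forms may sit there. But this article has a dedicated harms section and describes its approach as passive. The point concerns that stated approach.

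**Conclusion.** The concern holds in this form: the plan's stated route to individual harms is contact started by the participant, no reason for leaving is required, and stopping is tied in the text only to dropout. Under-counting is likely but not certain, and a low count would not be evidence of safety. The size cannot be fixed from the documents; the chance of no report runs from 0.001 to 0.72 under harm rates of 5% to 10% and reporting shares of 5% to 50%, all assumed. The conclusion itself needs only that not every harmed participant writes in. It should be acted on because the remedy is cheap and part of it needs no new data.

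**What to change.** Keep the right to leave without a reason.

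**If forms can still change:**

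1. Add one closed item with free text on unwanted effects since the last questionnaire to the existing posttreatment and follow-up web forms, in all three arms.
2. Add an optional reason-for-stopping link to the reminder email that non-responders already receive.
3. Tabulate dropout and any stated reasons by randomised arm.

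**Whether or not they can change,** report by randomised arm at 1 month, before the waitlist starts the app:

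1. the proportion whose K6 worsened from baseline, with the definition of worsening fixed before the data are examined;
2. the proportion reaching the protocol's own K6 cutoff of 13 or higher, as a descriptive count. Entry requires a screening score below 13, so some rise through regression to the mean is expected in every arm; the waitlist comparison allows for it;
3. dropout, beside these proportions, because they rest on responders.

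**If collection has ended,** as the abstract reports for late October 2023, also state that harms were not systematically elicited, and do not present low risk as a finding.

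The cost is a few seconds of participant time where forms can change, plus one extra table. No staff time with participants or extra visit is needed, and no clinical stopping rule is proposed.

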### Dissemination Plans

The findings of this study will be disseminated through presentations at national and international conferences and publications in international journals. The results of this research will adhere to the CONSORT (Consolidated Standards of Reporting Trials) statement [88].

### Ethical Considerations

The study protocol used in this study and all procedures were approved by the Life Science Research Ethics and Safety Committee of the University of Tokyo (22-326). Data collected in this study will be anonymized and managed. Written informed consent to participate will be obtained from all participants via a web form. Participants are given the option to opt out at any time. Participants will also be rewarded with a gift card worth up to JP ¥10,000 (JP ¥137.09=US $1 as of December 1, 2022), depending on their level of participation.

## Results

Recruitment of participants began in December 2022, and the intervention began in January 2023. A total of 375 participants have been enrolled as of September 2023. The intervention and data collection will be completed by late October 2023.

## Discussion

### Principal Findings

The purpose of this study is to develop a self-care app for MM and SCM and examine its effectiveness using various indicators such as work performance. The study will adopt an RCT design comparing the SCM and MM intervention groups and a waitlist group. This study will focus on accessibility and availability and will use a low-intensity self-care program delivered via a smartphone app. This will allow us to examine the possibility of supporting busy workers who have had difficulty participating in traditional intervention formats. It is expected that by developing accessible self-care smartphone apps and examining the effectiveness of the intervention, it will be possible to propose efficient and feasible solutions for improving workers’ mental health and work performance. In the field of worker assistance, where methodologically robust evidence is scarce [18], this study can contribute to the body of findings by examining the effectiveness of assistance through an RCT design.

In recent years, health support technologies using mobile digital devices, such as smartphones, have been developed, and their effectiveness has been examined; however, comparability between studies has been considered difficult [5]. Using consistent guidelines—such as the mobile health evidence reporting and assessment checklist [89]—when reporting the results of this study ensure that the findings from this study provide synthesizable evidence and promote comparability between studies.

### Strengths and Limitations

The study has several notable strengths. First, this study will adopt brief self-care interventions for preventive health care in healthy workers. Traditional self-compassion and mindfulness interventions are long-term face-to-face programs [8,21], thus presenting difficulties related to worker participation and dissemination [22]. For interventions aimed at treatment, evidence-based, structured programs for well-experienced instructors are essential. However, even a brief intervention with an app may be sufficient to facilitate preventive health care for healthy workers.

Second, this study will examine the intervention effects not only on mental health conditions but also on work-related outcomes and objective physiological measures, such as HR and HRV. Examining work-related outcomes can provide a broad perspective of the effects of interventions. Measuring objective physiological outcomes may provide insights into the mechanisms underlying these effects.

Third, this RCT design compares 2 types of interventions in the intervention group: SCM and MM. They are similar but have different background theories. This study on preventive health care for healthy workers has the potential to provide suggestive findings for the development of accessible, available, and more effective intervention content that can improve mental health and work-related outcomes.

This study has several limitations. First, the duration of the intervention is shorter, and the intensity is lower than that of traditional self-compassion and mindfulness interventions. Second, the intervention is conducted in a self-care format, which may result in a lack of sufficient skill acquisition and limited intervention effectiveness. Third, because the target population is limited to healthy workers, the intervention effect may be too small and not be fully confirmed. Furthermore, a trait mindfulness scale is not included in this study’s secondary outcomes. Measuring both, a self-compassion measure and a trait mindfulness scale would have provided a better understanding of each intervention’s effects and allowed us to determine any differences in the constructs being targeted. However, this is not possible in this study. Therefore, future research should use both a self-compassion measure and a trait mindfulness scale to better understand the intervention effects.

### Conclusions

The intervention protocol in this study has described an RCT to examine whether brief guided MM or SCM interventions provided by a smartphone app are effective for mental health and work-related outcomes among workers. The authors’ research team at the University of Tokyo, Japan, planned to begin the RCT in December 2022. There is a great need for preventive interventions for mental health and work-related problems such as presenteeism in the working population because of inadequate support. We expect that this study will contribute to the evaluation of effective self-care intervention content that will improve mental health, work performance, and related outcomes and promote mindful and self-compassionate attitudes when faced with distress.

## Appendix

Multimedia Appendix 1 App screenshot 1.

Multimedia Appendix 2 The CHERRIES (Checklist for Reporting Results of Internet E-Surveys) checklist.

Multimedia Appendix 3 App screenshot 2.

## Abbreviations

CFS: Cognitive Flexibility Scale
CHERRIES: Checklist for Reporting Results of Internet E-Surveys
CONSORT: Consolidated Standards of Reporting Trials
HR: heart rate
HRV: heart rate variability
K6: Kessler Psychological Distress Scale-6
MBI: mindfulness-based intervention
MM: mindfulness meditation
PANAS: Positive and Negative Affect Schedule
PSS-14: Perceived Stress Scale-14
RCT: randomized controlled trial
SCM: self-compassion meditation
SWLS: Satisfaction With Life Scale
WHO-HPQ: World Health Organization Health and Work Performance Questionnaire
